## Abstract

**Background:**

Gestational Diabetes (GDM) is one of the most common complications of pregnancies affecting around 7% of women. This clinical condition is associated with an increased risk of developing fetal macrosomia and is related to a higher incidence of caesarean section in comparison to the general population. Strong evidence indicating the best management between induction of labour at term and expectant monitoring are missing.

**Methods/Design:**

Pregnant women with singleton pregnancy in vertex presentation previously diagnosed with gestational diabetes will be asked to participate in a multicenter open-label randomized controlled trial between 38+0 and 39+0 gestational weeks. Women will be recruited in the third trimester in the Outpatient clinic or in the Day Assessment Unit according to local protocols. Women who opt to take part will be randomized according to induction of labour or expectant management for spontaneous delivery. Patients allocated to the induction group will be admitted to the obstetric ward and offered induction of labour via use of prostaglandins, Foley catheter or oxytocin (depending on clinical conditions). Women assigned to the expectant arm will be sent to their domicile where they will be followed up until delivery, through maternal and fetal wellbeing monitoring twice weekly. The primary study outcome is the Caesarean section (C-section) rate, whilst secondary measurement4s are maternal and neonatal outcomes. A total sample of 1760 women (880 each arm) will be recruited to identify a relative difference between the two arms equal to 20% in favour of induction, with concerns to C-section rate. Data will be collected until mothers and newborns discharge from the hospital. Analysis of the outcome measures will be carried out by intention to treat.

**Discussion:**

The present trial will provide evidence as to whether or not, in women affected by gestational diabetes, induction of labour between 38+0 and 39+0 weeks is an effective management to ameliorate maternal and neonatal outcomes. The primary objective is to determine whether caesarean section rate could be reduced among women undergoing induction of labour, in comparison to patients allocated to expectant monitoring. The secondary objective consists of the assessment and comparison of maternal and neonatal outcomes in the two study arms.

**Trial Registration:**

The study protocol has been registered in the ClinicalTrials.gov Protocol Registration System, identification number NCT01058772.

## Background

GDM is one of the most common complications of pregnancy and its incidence is estimated at 7% [1]. Among women affected by GDM, an increased rate of C-section has been observed, mostly unjustified [2,3]. Recent studies identified a C-section rate among women with this condition as high as 35% [4], and indicated a probability of undertaking a C-section in this group around 1.5 times the probability among non-GDM women [5].

Furthermore, babies born from women with GDM are significantly more exposed to perinatal risk, mostly related to fetal macrosomia [6]. This clinical condition is in fact associated to an increased risk of intrapartum traumatic lesions and asphyxia [7]. The incidence of macrosomia or birth weight above the 90^th ^percentile is more common among these women, in comparison to the general population [8]. These newborns, because of their peculiar intrauterine growth pattern, are characterised by a trunk mass larger than the head and consequently are more exposed to shoulder dystocia, bone fractures and brachial plexus injury, possibly with permanent outcomes [9,10].

The American College of Obstetricians and Gynecologists recommends a caesarean section for women with GDM and estimated fetal weight > 4500 g [11]. The American Diabetes Association recommends that GDM by itself is neither an indication for C-section nor for induction of labour before 38 completed gestational weeks [12]. Pregnancy prolongation beyond 38 weeks increases the risk to develop fetal macrosomia, without reducing C-section rate. As a result, delivery within the 38^th ^week of pregnancy is advisable if there are not other specific obstetric recommendations to determine an alternative management [12].

The guidelines currently in use are mainly based on retrospective studies and the experiences of single hospitals in the context of maternal and perinatal outcomes. As a consequence, there is ample possibility of variation in the clinical management of these women (expectant, induction or elective C-section) if determined by health professionals' individual preference [1]. To the best of our knowledge, only a randomized clinical trial [13] has been carried out and it has been included in the most recent Cochrane review investigating this issue [6]. Results of this trial suggested that expectant management after 38 weeks of pregnancy reduced Caesarean delivery rate and also increased the prevalence of large for gestational age newborns and shoulder dystocia [13]. Despite the importance of these results, this study was flawed by several methodological limitations. The randomization method and allocation concealment were not reported [10] and the sample population included both women with insulin-requiring gestational diabetes and class B pre-gestational. In addition, few non-randomized clinical trials [14,15] and small number of observational studies [8,16-19] have been published on this issue, but obvious methodological limitations interfered from drawing any definitive conclusions.

Strong evidence, based on adequately designed prospective studies and randomized controlled trials, in favour or against the effectiveness and safeness of induction in women with GDM are missing [1,10]. In light of this clinical dilemma, we propose a multicenter randomized controlled trial comparing induction of labour at 38-39 gestational weeks to careful expectant monitoring.

## Methods/Design

The proposed research regards a multicentre open label randomized controlled trial in women with GDM between 38+0 and 39+0 gestational weeks. The study will be carried out by the GINEXMAL Study Cooperative Research Group including 9 Teaching Hospitals, 5 in Italy and 4 abroad. The Institute for Maternal and Child Health - IRCCS Burlo Garofolo (Italy) together with The Helen Schneider's Hospital for Women - Rabin Medical Centre (Israel) will be the coordinating centre of the research project.

A total sample of 1760 patients (N = 880 per intervention group) will be recruited. The sample size has been estimated to be sufficiently large to achieve significant results with concerns to the main outcome of the study. In particular, it will be able to demonstrate a difference between the two arms ≥ 6% (31% of C-section in the expectant group and 25% in the induction group; relative difference between the 2 groups equal to 20% in favour of induction [13]), considering α error equal to 5% and 80% power.

Randomization will be centralized and coordinated by the Epidemiology and Biostatistics Unit (IRCCS Burlo Garofolo, Italy) using a computer-based method. The randomization list will be blocked (using blocks with a size of 10) and stratified by centre. The allocation concealment will be guaranteed through the use of closed opaque envelopes, consecutively numbered. In each envelope a patient's allocation group will be indicated, based on randomization. The study will be an open label trial because of the practical impossibility to blind either health professionals or patients to the allocation group.

Medical personnel directly involved in the management of the patient, will open the first available envelope and assign the patient to the corresponding randomization group (experimental group: induction of labour or control group: expectant management). The recruitment phase of the study will last 2 years.

Women older than 18 years of age with a singleton pregnancy in vertex presentation diagnosed with GDM in their current pregnancy will be eligible. Gestational diabetes mellitus is defined as carbohydrate intolerance, with onset or first recognition during pregnancy [20,21]. Diagnosis will be based upon abnormal 50 gr Glucose Challenge Test (GCT) (> 140 mg/dl) followed by 2 abnormal indices in the Oral Glucose Tolerance Test (OGTT) (according to Carpenter & Coustan Criteria). Women with GCT > 200 mg/dl will undergo 100 gr OGTT as well. If prior to the beginning of the study initial HAPO study consensus is available [21], diagnosis of GDM will be based on these criteria. Patients characterised by the mentioned eligibility criteria (Table 1) will be asked to take part in the study during a consultation at the Outpatient clinic at approximately 35 weeks of gestational age. At the consultation the patient will first have the protocol explained verbally. In order to give the individual an opportunity to consider the proposed proceedings, they will be left with a paper copy of the protocol for a short period of time. If the patient expresses a desire to take part, she will then be referred to the Day Assessment Unit between 38+0 and 39+0 weeks of gestational age.

**Table 1 T1:** Inclusion and Exclusion Criteria

Inclusion Criteria
Maternal age ≥ 18 years
Singleton pregnancy in vertex presentation
Gestational age between 38 and 39 weeks verified by LMP and confirmed by first trimester ultrasound
Women diagnosed with GDM in the present pregnancy
No other contraindications to vaginal delivery

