**Figure 1 F1:**
[figure not shown]
**Trial Flow chart**.

Patients enrolled in the conservative management arm will be followed up twice weekly by Electronic Fetal Heart Rate monitoring and Biophysical profile (Figure 1). Patients will be followed up until 41+0 gestational weeks. Women, who will not deliver by this gestational age, will be admitted for labour induction (see the protocol above). Induction of labour will be offered when non-reassuring fetal status is suspected. All patients in the conservative arm will undergo fetal weight ultrasound estimation prior to induction. Patients with estimated fetal weight over 4000 gr will be offered a caesarean section.

General information on recruited patients, outcomes and randomization group will be indicated in an appropriate paper questionnaire in the first instance and then reported on an electronic database accessible from different study sites in the second instance. In each participating centre, medical personnel will fill up the electronic form directly. Data will be kept anonymous and will be analyzed by the Epidemiology and Biostatistics Unit - IRCCS Burlo Garofolo, using STATA 9 statistical package. Continuous variables will be reported as mean and standard deviation, categorical variables as proportions and percentages. The two groups will be compared by their main characteristics to evaluate the efficacy of the randomization process. To evaluate the main outcome of the study, C-section incidence will be compared between the two groups using the χ^2 ^test. Possible confounders such as: blood glucose control, obesity, participating centre policy etc. will be controlled through multivariate analysis (logistic regression). To compare secondary outcome variables between the two groups, the ANOVA technique will be used for continuous variables and χ^2 ^test for categorical. Statistically significant differences will be determined by a p-value inferior to 0.05. Although crossovers between the two allocation groups could complicate data interpretation, it is impossible to prevent them. However, data will be analysed by intention-to-treat. Finally, a sensitivity analysis will be carried out to confirm that results do not change significantly despite the variety of populations included in the study.

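### One published block size of 10 per centre, with treating staff opening numbered envelopes in an open-label trial, leaves up to one allocation in six predictable, so concealment is not guaranteed

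*Protocol article*

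**What the plan says.** All the elements are in the Protocol article, Methods/Design.

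- **List:** "The randomization list will be blocked (using blocks with a size of 10) and stratified by centre". No other block size is mentioned.
- **Coordination:** "Randomization will be centralized and coordinated by the Epidemiology and Biostatistics Unit". This describes how the list is generated and managed; the assignment itself takes place at the site.
- **Concealment:** "The allocation concealment will be guaranteed through the use of closed opaque envelopes, consecutively numbered".
- **Assignment:** "Medical personnel directly involved in the management of the patient, will open the first available envelope".
- **Masking:** "The study will be an open label trial because of the practical impossibility to blind either health professionals or patients to the allocation group".
- **Size:** "A total sample of 1760 patients (N = 880 per intervention group) will be recruited", with a research group "including 9 Teaching Hospitals, 5 in Italy and 4 abroad".

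The same section puts enrolment between 38+0 and 39+0 weeks. The fetal weight estimate and the Bishop score are obtained on the day of enrolment, and written consent comes before allocation. Women with an estimated weight above 4000 g or a Bishop score above 7 are excluded. The sites also share "an electronic database accessible from different study sites".

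**The concern.** An opaque envelope stops staff from reading an allocation. It does not stop them from inferring one. With a constant, published block size, the envelope number gives the position in the block. Because treatment is unmasked, past allocations give the count in each arm. Once five of either arm have been used, every remaining envelope in that block is known. The claim that the envelopes guarantee concealment is therefore too strong.

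Staff who expect a given arm have two routes to selective enrolment. They can defer a woman within the one-week window, or they can let the expectation colour the consent discussion or the judgement of eligibility. Just before allocation they know two features that bear on caesarean section under this protocol. Failure of the cervix to ripen can lead to an offer of a section, and in the expectant arm so can an estimated fetal weight over 4000 g before induction. The Background section itself says that management varies with professional preference.

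The primary outcome is an unblinded clinical decision, and the planned difference is 6 points. Selection before allocation makes the arms differ at baseline. Intention-to-treat analysis keeps the arms as enrolled, so it cannot undo this.

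**Working it through.** **Inputs from the Protocol article (Methods/Design):** block size 10, so 5:5 under equal allocation (m = 5); 1760 women; 9 centres; 2 years' recruitment; caesarean rates 31% and 25%; alpha 5%; power 80%.

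**The plan's own figure.** The article gives no figure for predictability. Its sample size reproduces: two-sided 5%, 80% power, pooled variance under the null and no continuity correction give 878 per arm, and 880 per arm has 80.1% power. The concern does not touch the sample size.

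**Step 1: allocations known with certainty.** In a block of 2m these are the final run of one arm. Its expected length is 2m/(m + 1) = 10/6 = 1.67 per block, or 16.7%. Over the trial, 1760 × 0.1667 = 293. Listing all C(10,5) = 252 possible blocks gives the same 1.67.

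**Step 2: best-guess rate.** The best strategy is to guess the arm with more places left. Expected correct guesses = m + (4^m / C(2m,m) − 1)/2 = 5 + (1024/252 − 1)/2 = 5 + 1.53 = 6.53 of 10, or 65.3%, against 50% by chance. The full listing agrees.

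**Step 3: comparison of fixed sizes.**

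| Fixed block | Certain | Best guess right |
|---|---|---|
| 4 | 33.3% | 70.8% |
| 6 | 25.0% | 68.3% |
| 8 | 20.0% | 66.6% |
| 10 | 16.7% | 65.3% |

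Ten is the least predictable of these. The weakness is the combination of a fixed and disclosed size, centre strata, no masking and local opening.

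**Step 4: pace of recruitment.** Assuming equal recruitment over 104 weeks, 1760/9 = 196 women (about 20 blocks) per centre, or 196/104 = 1.9 women per centre per week. About two envelopes therefore pass during one woman's window.

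**Step 5: possible bias (illustration; the shift is assumed and stands nowhere in the article).** If baseline risk differs between arms by 10 to 20 points in the certain allocations only, bias = 0.167 × 10 = 1.7 points to 0.167 × 20 = 3.3 points. With no true effect and 28% in both arms (the midpoint of 31% and 25%), the standard error is √(2 × 0.28 × 0.72/880) = 2.14 points. The nominal 5% error then becomes about 12% to 34%.

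**Step 6: effect of varying the block size.** Sizes 6, 8, 10 and 12 in random order were simulated against an optimal guesser who knows the set of sizes but not the order. About 1% of allocations are certain, and the best guess is right about 65.6% of the time.

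**The case against.** **The predictability figures are upper bounds.** They assume a recruiter who knows every earlier allocation at the centre. The article has the obstetrician on call explain the study, which suggests rotating staff who would know less. This stands.

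**Deferral is a limited tool.** All certain allocations at the end of a block belong to one arm, and the envelope after them opens a new block at 50:50. Deferring past them avoids an arm but does not secure the other one. At about 1.9 women per centre per week few envelopes pass in the window, and a woman sent away may go into labour or leave it. This stands too. It weakens deferral, but not influence through consent or eligibility.

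**The risk shift is assumed, and it is large.** Around 28%, a 20-point gap means enrolling women at about 18% risk for one arm and 38% for the other, in the same direction at every centre. Opposing preferences could partly cancel. The exclusions also narrow the range: steering on fetal size is possible only up to 4000 g. A reader might infer from the bias figures that the result will be distorted, but the article gives no evidence of steering and no basis for a likely size.

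**There are partial safeguards.** Consent precedes allocation, baseline characteristics will be compared, and logistic regression is planned. These help to detect a problem, but they do not prevent it. The article does not name Bishop score or fetal weight among the adjustment variables.

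**Conclusion.** The concern holds as a weakness of concealment. The stated procedure does not guarantee concealment, because for a recruiter who tracks the whole centre up to 16.7% of allocations (about 293 of 1760) are certain and the best guess is right up to 65.3% of the time. These figures follow from the block size alone and need no assumption about risk.

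The size of any resulting bias is unknown. The 1.7 to 3.3 points rest entirely on the assumed shift and should be read as a scenario. Two stronger readings are not supported: that staff can wait until the envelope suits them, and that selective enrolment is to be expected. Nothing in the article is contradictory or miscalculated. This is a design weakness that is cheap to correct before enrolment and cannot be repaired afterwards. It should be fixed.

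**What to change.** Make two changes before the first woman is enrolled.

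1. **Replace the fixed blocks with randomly varying sizes**, for example 6, 8, 10 and 12, still stratified by centre. Keep the sizes out of every document that sites can read. This takes certain allocations from 16.7% to about 1%. It does not lower the best-guess rate, which stays near 65%, so it is not sufficient alone. A smaller fixed block would make matters worse.
2. **Release each allocation one at a time through the existing electronic database**, only after consent, eligibility, estimated fetal weight and Bishop score have been entered and locked. A predicted allocation can then no longer alter the recorded eligibility data, and every assignment is fixed in order and time.

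The cost is a new list, a small database function and a slightly larger possible imbalance between arms in small centres. Deferral before any data are entered is not fully prevented.

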**Exclusion Criteria**

Pre-GDM
Prior C-section
Suspected estimated foetal weight > 4000 g at enrolment
Any known contraindications to vaginal delivery
Uncertain gestational age
Non reassuring foetal wellbeing necessitating delivery
Maternal pregnancy-related disease necessitating delivery
Bishop score > 7 at enrolment
Known foetal anomaly

If there are no other contraindications to deliver vaginally, patients will be enrolled between 38+0 and 39+0 weeks of gestational age (verified by last menstrual period (LMP) and confirmed by first trimester ultrasound). In the case of a discrepancy, gestational age assessed by ultrasound in the first trimester will be considered as the true reference. Uncertain gestational age or any major fetal anomaly will cause exclusion from the trial (Table 1). Women diagnosed with pre-gestational diabetes or demonstrating a prior C-section in their obstetrical history will be excluded. The identification of non-reassuring fetal status assessed by cardiotocography alone or as a formal part of a biophysical profile [22] or the presence of maternal or fetal conditions complicating pregnancy (e.g. severe preeclampsia/HELLP Syndrome or severe fetal growth restriction) and requiring immediate obstetrical intervention (prompt delivery or prompt C-section) will lead to the patient's exclusion.

After careful evaluation of inclusion and exclusion criteria (Table 1), suitable patients will have been identified. On the day of enrolment, an ultrasound assessment of fetal weight, as well as a Bishop score evaluation, will be performed. Whenever the estimated fetal weight exceeds 4000 gr, patients will be excluded from the trial and offered a C-section. A Bishop score greater than 7 will automatically exclude the patient from the trial. Furthermore, an attentive evaluation of possible contraindications to vaginal delivery and an assessment of fetal wellbeing through a cardiotocographic trace will be carried out at enrolment. The remaining inclusion/exclusion criteria will be assessed through the evaluation of the patient's current and past obstetric records.

Eligible women will be provided a comprehensive explanation of the project by the obstetrician on call, in terms of study procedures and risks versus benefits attached. Patients wishing to take part will be asked to sign a written consent form before being allocated to the randomization group.

Data about obstetric history will be collected through consultation with the patient and evaluation of the patient's previous records and clinical reports. The outcomes will be evaluated during delivery and until maternal and neonatal discharge. Perinatal and maternal deaths will be identified until discharge. Perinatal deaths should include events up to 7 days after birth and most newborns will be discharged earlier. Our assumption is that perinatal death would occur almost exclusively in newborns manifesting complications during admission and consequently this could be accurately estimated by the time of discharge. At enrolment, patients assigned to the induction group will be admitted to the obstetric ward (Figure 1). Induction of labour will be performed by using dinoprostone, 2 mg vaginally, or dinoprostone, 0.5 mg intracervically, in 6-8 hour intervals (up to 5 doses) or dinoprostone, 10 mg vaginal device. Once the patient's Bishop score exceeds 7 or regular contractions are diagnosed, patients will be transferred to the delivery ward for artificial rupture of membranes (ARM) or oxytocin augmentation as indicated. Patients, in which cervical ripening does not occur (Bishop score < 7) after 5 attempts with Prostaglandin E2 (PGE2), will be offered either oxytocin or Foley catheter induction or C-section, according to local protocols.

